**4.4 Sample Size Estimation**

For the quantitative data analyses, to examine changes in UAI with HIV-negative or unknown serostatus partners, random coefficient regression (also known as multilevel modeling) analyses will be conducted. The random regression model employs time as a within-subjects variable, and subject-specific intercepts and slopes for the time effect (i.e., trajectories) are summarized with mean and variance parameters. The analysis has several important advantages. It accounts for serial correlation within subjects, is relatively robust to randomly missing data, and can incorporate certain non-random missing data, especially those arising from drop-outs, without biasing model estimates. Following the approach for trajectory modeling outlined by Muthén & Muthén (2002), power analyses suggest an N=40 to detect a meaningful average change (i.e., medium effect size) in UAI with =.05, and 1-=.80. Given that the groups will have 6 persons each, with 7 groups, the final sample size will be N=42.

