**4.9.3 Quantitative Measures**

The quantitative measures used in this study have been demonstrated to possess good reliability and validity, as well as documented associations with risky sexual behaviour23,51,52,59,60. It is anticipated that the entire protocol will take approximately 50 minutes to complete at each timepoint: baseline, post-intervention, and 3 months after the end of the intervention.

**Demographics Questionnaire.** Participants will complete a demographics questionnaire assessing age, ethnic/racial background, religious affiliation, educational level, living situation, marital/partner status, socioeconomic status, and sexual orientation.

**Primary Endpoint Variable: Unprotected Sexual Behaviour.** Participants will be asked to indicate their frequency of unprotected anal intercourse with HIV-negative or unknown HIV status partners in the past 3 months.

**Secondary Endpoints.** Secondary endpoints will also examine protected and unprotected 1) insertive and receptive anal intercourse with men, 2) anal and/or intercourse with women with and without a condom in the previous 3 months with partners who were HIV+, partners who were HIV-negative, and partners of unknown serostatus. Second, participants will be asked to indicate their number of HIV+ partners, HIV-negative partners, and partners of unknown serostatus in the previous 3 months. Third, participants will be asked if they had insertive or receptive anal intercourse or vaginal intercourse with their last sex partner, as well as their last partner’s serostatus.

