**Potential Theoretical Mediators.** Per the IMB model, Information, Motivation, and Behavioural Skills will be assessed to examine the relative effects of each component on UAI with non-HIV+ partners. The HIV-Knowledge Questionnaire-1876 will be used to assess knowledge of basic HIV information. Questions will also ask about knowledge of very recent data, such as the PHAC’s statement on the Swiss Cohort Study77, and knowledge of criminalization of unprotected sex for HIV+ individuals (CITES). Participants’ motivations to perform 8 risk-reduction actions will be assessed per recent research assessing the IMB model60. Examples of items include intentions to keep condoms nearby, to use a condom with a new sexual partner, and to use a condom when drunk or high on a substance. Self-efficacy for behavioural skills in risk reduction will be assessed using a 6-item measure60. Items include “I am certain I can use a condom with my main sex partner.” Participants will also be asked about whether they have engaged in 5 risk reduction behavioural skills over the past month, such as refusing to have unsafe sex and guiding sex toward safer sex behaviour.

**Additional Measures.** Due to data implicating substance use in unprotected intercourse among MSM**38**.**78-81**, participants will indicate how many times they have been intoxicated when drinking alcohol or used an injection or non-injection substance in the past 3 months. To assess for possible confounding due to social desirability reporting bias on sensitive behaviours such as sexual behaviour and drug use, participants will complete the Marlowe Crowne Social Desirability Scale - Short Form81. If any of these variables is associated with unprotected sexual behaviour, they will be examined as potential other mediators in analyses examining the effect of the intervention on unprotected anal intercourse with HIV-negative or unknown HIV status partners. CD4 count and viral load will be requested through self-report for the present study. These measures will serve as medical indices of severity of HIV illness in our HIV+ sample.

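### Social desirability is collected to check for reporting bias but is then assigned the role of a possible mediator of the intervention effect

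*Protocol*

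**What the plan says.** Under Additional Measures, Protocol section 4.9.3 gives the reason for including the Marlowe-Crowne short form: "To assess for possible confounding due to social desirability reporting bias on sensitive behaviours such as sexual behaviour and drug use". The next sentence fixes how the additional measures will be analysed: "If any of these variables is associated with unprotected sexual behaviour, they will be examined as potential other mediators". The outcome named for that analysis is the primary endpoint.

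The word *other* points back to the preceding paragraph on theoretical mediators, which covers the information, motivation and behavioural skills (IMB) constructs: "Information, Motivation, and Behavioural Skills will be assessed to examine the relative effects of each component on UAI with non-HIV+ partners".

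Two further statements set the context. The primary endpoint is self-reported: "Participants will be asked to indicate their frequency of unprotected anal intercourse with HIV-negative or unknown HIV status partners in the past 3 months" (section 4.9.3). The effect is a change over time within men: "The random regression model employs time as a within-subjects variable" (section 4.4). Every participant receives the six sessions (section 4.2), and no comparison group is described. Nowhere does the protocol give the scale a role as covariate, adjustment variable or sensitivity variable.

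**The concern.** A mediator is a step through which an intervention changes behaviour. Reporting bias is an error in the measured outcome. The protocol names the second as the reason for collecting the scale and then plans to examine it as the first.

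The stake is how the study's main product, an effect size for a later randomised trial (sections 1.0, 3.0 and 5.0), will be read. With no comparison arm, a shift in how men report is not cancelled out. Such a shift is plausible from the protocol's own content: the programme covers the legal position on unprotected sex without disclosure (section 2.3.2), and the assessments ask about criminalization (section 4.9.3). If reporting changes, part of the apparent fall in UAI could be presented beside the IMB constructs as a route by which the intervention worked, and the headline change would carry no correction.

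**Working it through.** The protocol states no figure on this point, so there is none to reproduce. The check is a reading of the text followed by an illustration.

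**1. Purpose against role.** The purpose is confounding by reporting bias. The role, if the scale is associated with unprotected sex, is that of a further mediator. Both stand in adjacent sentences of section 4.9.3.

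**2. Is a mediator role possible?**
- *Stable trait.* The intervention does not move the score, so no effect passes through it. The score could still matter if men with high scores change their reports more, which is an interaction with time.
- *Score rises after the groups.* An indirect effect then exists arithmetically, but it consists of lower reporting and not of lower risk behaviour.

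The mediator label is wrong in both cases.

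**3. Illustration of the second case.** All inputs except N = 42 (section 4.4) are assumptions.
- Score: SD 1 at each visit, correlation 0.8² = 0.64 between visits, mean rise *a* after the groups.
- Report: Y = T − 0.5·S + e, where T is true behaviour, constant within a man; S is the score; e has SD 0.5.
- Change: D_Y = −0.5·D_S + (e₁ − e₀), so the expected change is −0.5·a.
- Indirect part: b × mean(D_S), with b = cov(D_Y, D_S)/var(D_S). Adjusted part: mean(D_Y) minus the indirect part.

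Results over 4,000 simulated trials with no true change in behaviour:

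| Rise in score (SD) | Expected change | Simulated total | Indirect via score | Adjusted | Unadjusted test significant (two-sided .05) |
|---|---|---|---|---|---|
| 0 | 0 | 0.00 | 0.00 | 0.00 | 4.5% |
| 0.3 | −0.5 × 0.3 = −0.15 | −0.15 | −0.15 | 0.00 | 21% |
| 0.5 | −0.5 × 0.5 = −0.25 | −0.25 | −0.25 | 0.00 | 50% |

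In standardised terms, var(D_S) = 2 × 0.6² = 0.72 and var(D_Y) = 0.25 × 0.72 + 2 × 0.25 = 0.68, so the SD of change is 0.825. The artefact is 0.15/0.825 = 0.18 to 0.25/0.825 = 0.30 SD of change.

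**4. Would a baseline score alone repair this?** Under the same assumptions E(S₁ | S₀) = a + 0.64·S₀, so E(D_Y | S₀) = −0.5·(a − 0.36·S₀).
- At the mean baseline score the change is still −0.15 or −0.25, so the artefact is untouched.
- At one SD below the mean it is −0.5 × (0.3 + 0.36) = −0.33 or −0.5 × (0.5 + 0.36) = −0.43. Regression to the mean makes it larger.

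The change in score has to be in the model. Section 4.9.3 gives one completion time for the whole set of measures at baseline, post-intervention and 3 months, which implies that the scale is repeated.

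**5. The association condition.** The protocol gives no rule for deciding that a variable is associated with UAI. If it were a two-sided .05 test of a correlation (assumption), power at N = 42 by Fisher's z is:
- r = 0.3: 0.3095 × √39 = 1.93; Φ(1.93 − 1.96) ≈ 49%
- r = 0.2: 0.2027 × √39 = 1.27; Φ(1.27 − 1.96) ≈ 24%

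A real association could easily fail the screen, and the scale would then never be examined.

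**The case against.** The strongest reply is that a mediation model conditions on the scale. Its direct effect is the change not related to social desirability, which is the adjusted column above. A careful analyst could therefore find the artefact with the planned analysis. This stands. A reader might infer that the plan cannot reduce or reveal reporting bias at all; the documents do not support that. The fault lies in the assigned role and in the reading it invites.

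The analysis is also conditional and exploratory. The protocol speaks of potential mediators and never says that a path through this scale would be claimed as benefit, so misattribution is a risk and not a stated intention. The time model in section 4.4 is not altered by it. There is other protection too: code numbers instead of names (section 4.8.1), questionnaire administration (section 4.10.2), and qualitative interviews meant to clarify the quantitative results (section 4.9.2). None of these corrects the estimate, but the setting is less bare than the mediator sentence alone suggests.

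Two wider readings should be resisted. The sentence also covers substance use, for which a mediator role is plausible. And the statement that the IMB measures "will be assessed to examine the relative effects of each component on UAI with non-HIV+ partners" might be taken as a claim to separate the effects of intervention components that every man receives. It stands under theoretical mediators and concerns measured constructs, so at most its wording is loose, and it is a separate matter.

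That a statistical analysis plan may exist does not remove the point. The protocol has not left the role open; it has fixed one that conflicts with its stated purpose.

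**Conclusion.** The point holds as a conflict between the purpose and the analytic role of one scale. The textual conflict is clear on the natural reading of two adjacent sentences. Its consequence is conditional: it needs an association with unprotected sex, a score that moves after the groups, and an indirect effect read as benefit.

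The size cannot be taken from the protocol. Under the assumptions above it is 0.15 to 0.25 units of reported UAI for a rise of 0.3 to 0.5 SD in the score, and zero if the score does not rise. The illustration favours adjustment, because it assumes that the scale captures the reporting tendency fully. A shift in reporting that the scale does not register would remain under any of these models.

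**What to change.** In section 4.9.3, separate the two kinds of variable. Keep substance use as a candidate mediator and remove social desirability from that list.

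Pre-specify, without a significance screen, a sensitivity version of the UAI time model, using whichever form of the endpoint section 4.10.3 leads to (raw, log-transformed or dichotomised). It should include:
- the baseline social desirability score;
- its interaction with time;
- the within-person change in score at each visit.

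State that the scale is completed at all three assessments. Report the UAI change with and without this adjustment, and state that no part related to social desirability will be interpreted as intervention benefit.

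The cost is a change of wording and one extra model on data that appear to be collected already. The model uses a few degrees of freedom, and the interaction will be imprecise at N = 42, so the adjusted result should be presented as a sensitivity estimate with its interval.

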**4.10 Stages of the Study**

**4.10.1 Research Stage I – Study Initiation**

In Month 1, the study coordinator and 2 group facilitators from our previous Ontario HIV Treatment Network START grant on Poz Prevention will be re-hired. The project timeline can be found in Appendix 2. Both facilitators are HIV+ gay men with extensive experience with group facilitation. Through the START grant, our facilitators have been trained by [name] of the Centre for Addiction and Mental Health in motivational enhancement counselling techniques for HIV prevention. Program staff will be trained in study participant recruitment, administration of self-report measures, and data entry. Procedures for all aspects of project management will be established and implemented during the first 3 months of the project. A weekly planning meeting of staff and investigators will be initiated to begin development of project infrastructure. Staff will regularly coordinate with [name] to ensure efficiency in participant recruitment. A protocol manual will be created for conducting all aspects of the study, including detailed information on participant eligibility criteria, recruitment procedures, informed consent procedures, administration of research measures, and data management plans. Standardized project forms also will be created (e.g., protocol checklists). In addition, facilitators will be trained that if a participant experiences distress at any time, referrals for counselling will be ready at hand. Intervention program facilitators will be trained in group facilitation and will be knowledgeable about referral sources for HIV+ group members who seek information or counselling, and the project will be housed at the AIDS Committee of Toronto which has HIV-related counselling and information resources. Program delivery staff/trainees will be supervised by [name].

**4.10.2 Research Stage II – Data Collection**

Data collection will begin in month 4 of Year 1 and will continue through month 6 of Year 2 of the study. Persons in the study who contact the study office will be informed about the opportunity to participate in the study while waiting for their appointments. Specifically, they will be told that the study is involves a series of workshops intended to improve sexual health among HIV+ MSM, that participation entails responding to several questionnaires and a brief interview at a baseline assessment taking about 120 minutes to complete, a series of 6 workshops of 90 minutes each, a post-intervention assessment of 60 minutes, and a 3-month follow-up of 120 minutes. They will also be told that $30 per hour will be provided in exchange for participation. [name] have found these recruitment procedures to be both unobtrusive and effective in other larger scale studies of HIV+ MSM.

Upon obtaining informed consent, quantitative measures will be administered in questionnaire format. Upon completion of the protocol, participants will be debriefed and given the opportunity to ask any questions. Participants will then be remunerated at $30 per hour. Qualitative interviews will explore in greater depth the evaluative questions in 4.9.2 above and also the degree to which the workshops resonated with participants’ everyday lives by asking about decision-making in recent sexual encounters.

**4.10.3 Research Stage III – Data Entry and Analysis**

The study coordinator will oversee data management procedures established in study stage I once data collection has begun. Data entry and analysis will proceed until month 9 of Year 2 of the study. Statistical analysis will be conducted under the guidance of the quantitative psychologist of the study team, [name], who is well-trained in analyses of behavioural intervention data. Completed protocols will be stored in a locked file cabinet and only assigned participant identification numbers will appear on completed assessment materials to protect confidentiality. A data file will be created using SPSS or STATA into which coded data will be entered. If the primary endpoint is not normally distributed, it will be transformed using the formula [log10 (x +1)]82 to avoid violations of assumptions of normality in parametric analyses. If this does not sufficiently correct for positive skew or kurtosis, data will be dichotomized per standard convention in the HIV behavioural literature into presence or absence of unprotected sex with non-HIV+ partners in the past 3 months.

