**3.0 PRINCIPAL AIMS AND HYPOTHESIS OF THE PRESENT STUDY**

The current study will investigate an HIV prevention intervention for HIV+ MSM. This Phase II trial will determine the effect size of the intervention, while incorporating one aspect of a Phase I trial by examining the tolerability of the intervention among HIV+ MSM. The present study is intended to be a rigorous evaluation of the HIV prevention intervention, with the ultimate aim of evaluating the efficacy of the intervention using a Phase III randomized control trial (RCT), per standard procedures for evaluating health interventions74**.**

The study hypothesis is that the study intervention will result in reduced prevalence of unprotected anal intercourse (UAI) with partners who are HIV-negative or unknown serostatus.

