**4.3 Sample**

Individuals will be eligible to participate in the intervention if they: (1) are HIV+ men who report UAI with a partner of HIV-negative or unknown HIV status in the past 3 months; (2) speak and understand English, (2) anticipate that they will be able to attend all workshops; and (3) are willing to participate in program monitoring and evaluation. Persons will be excluded if it is found that their ability to respond to study measures could be compromised by 1) central nervous system conditions (e.g., advanced HIV-associated dementia), 2) acute psychotic conditions, 3) acute mood dysregulation (e.g., manic states), and/or 4) debilitating physical conditions. For ethical reasons, all participants may withdraw from the research component of the study while still remaining in the intervention. Based on the literature, we anticipate that a number of participants will display psychological or other lifestyle characteristics that are strongly associated with sexual risk taking. They will be offered referral to counselling where appropriate; however, the decision to pursue such additional support will be left with the individual men and will not influence their eligibility to participate in the intervention. To avoid conflict of interest, participants who are given referrals will be referred to counselling with providers outside the study team. In addition, if a participant experiences distress at any time, referrals for counselling will be ready at hand. Intervention program facilitators will be trained in group facilitation and will be knowledgeable about referral sources for HIV+ group members who seek information or counselling, and the project will be housed at the AIDS Committee of Toronto which has HIV-related counselling and information resources.

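### The dichotomised fallback for the primary endpoint starts at about 100% by eligibility, so it can show only no change or a fall, and a single arm cannot tell that fall from regression to the mean

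*Protocol*

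**What the plan says.** Four parts of the protocol bear on this point.

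- **Eligibility (section 4.3).** Participants "are HIV+ men who report UAI with a partner of HIV-negative or unknown HIV status in the past 3 months".
- **Primary endpoint (section 4.9.3).** The declared variable is the "frequency of unprotected anal intercourse with HIV-negative or unknown HIV status partners in the past 3 months", collected at baseline, post-intervention and 3 months after the intervention ends.
- **Handling of non-normality (section 4.10.3).** The endpoint is first transformed as log10(x+1). "If this does not sufficiently correct for positive skew or kurtosis", then "data will be dichotomized per standard convention in the HIV behavioural literature into presence or absence of unprotected sex with non-HIV+ partners", again over the past 3 months.
- **Hypothesis (section 3.0).** The intervention is expected to lead to "reduced prevalence of unprotected anal intercourse (UAI) with partners who are HIV-negative or unknown serostatus".

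The model is a random coefficient regression over time, in which "subject-specific intercepts and slopes for the time effect (i.e., trajectories) are summarized with mean and variance parameters" (section 4.4). All participants receive the intervention, in 7 groups of about 6, giving N=42. A randomised comparison is left to a later trial (sections 3.0 and 4.11). The protocol does not comment on the overlap between the entry criterion and the dichotomised endpoint, and it gives no rate at which men would stop reporting the behaviour without intervention.

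**The concern.** The entry criterion and the binary fallback are the same yes/no question about the same recall window. Answering yes is the condition for being in the study, so the baseline is fixed by selection and carries almost no information. Any man who has no such encounter in a later 3-month window, for whatever reason, counts as improvement, and no man can count as a deterioration from baseline.

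This matters because the study exists to supply an effect size for designing a randomised trial. A change in prevalence measured from a baseline of 100% mixes intervention effect with regression to the mean, and there is no comparison group to subtract the latter. The hypothesis adds to the risk: it is worded as prevalence, which is the binary quantity, whereas the declared primary endpoint is a frequency. A reader of section 3.0 would expect the dichotomised result to be the main one.

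**Working it through.** **Inputs.** N=42 (section 4.4). Binary baseline 42/42 (sections 4.3 and 4.10.3 together), apart from any gap between screening and baseline or inconsistent reporting. No intervention effect. The lapse rate q, the chance that a man who was positive at baseline reports none in a later 3-month window, is an assumption, because the documents give none; q is varied from 5% to 30%. Men are treated as independent.

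**The plan's own figure.** 7 × 6 = 42 is correct. The N=40 behind it is for a medium average change and cannot be reproduced from the stated inputs: a paired comparison with an assumed standardised effect of 0.5, two-sided 0.05 and 80% power needs (1.960 + 0.842)² / 0.5² = 31.4, so 32, or 34 with the t distribution. The standard deviation, within-person correlation and dropout are not stated, so N=40 can be neither confirmed nor called wrong. Either way, it is not stated for a binary endpoint with a fixed baseline.

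**Observed fall.** One man in 42 reporting none is enough, so P(fall) = 1 − (1 − q)^42.

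**Significant fall.** Exact McNemar serves as an illustration. With baseline at 100%, all discordant pairs go one way, so with D movers the two-sided p is 2 × 0.5^D. D=5 gives 0.0625 and D=6 gives 0.031, so 6 movers are needed. P(significant) = P(X ≥ 6) with X ~ Binomial(42, q).

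| Assumed lapse rate q | Expected movers, 42q | P(observed fall) | P(significant fall) |
|---|---|---|---|
| 5% | 2.1 | 88% | 2% |
| 10% | 4.2 | 98.8% | 24% |
| 15% | 6.3 | 99.9% | 62% |
| 20% | 8.4 | 99.99% | 87% |
| 30% | 12.6 | over 99.99% | 99% |

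**What q might be.** The protocol's prevalences give a rough guide if a period-to-period correlation ρ is assumed, using q = (1 − prevalence) × (1 − ρ). For 37.6% (section 1.0) and ρ = 0.5, 0.7, 0.9, q is 31%, 19%, 6%, and P(significant) is 99.7%, 82%, 4%. For about half (section 4.5), q is 25%, 15%, 5%, and P(significant) is 97%, 62%, 2%. The correlations are assumed, so this shows a range and is not an estimate.

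**The planned type of model.** No-effect data were simulated for 42 men at three times, with baseline all 1 and 40 runs per setting. With time categorical, the baseline logit has no finite maximum-likelihood estimate: ordinary logistic fits failed or gave unusable standard errors in 95–100% of runs, and random-intercept fits drifted to baseline intercepts of about 24–39. With time linear, random-intercept fits were usually finite. GEE with linear time then declared a significant decline in about 80%, 98% and 100% of runs at q = 10%, 20% and 30%. Random slopes were not tested.

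**Does a count analysis escape?** Only in part. Entry requires a baseline count of at least 1, while later counts may be 0. In no-effect simulations of overdispersed counts with assumed parameters, the follow-up to baseline ratio was between 0.82 and 0.99, depending on those parameters. In one such set, a negative-binomial GEE (dispersion fixed at 1) gave a significant fall in 7–16% of runs against a nominal 2.5%; binary McNemar gave one in 76–99.7% of the same runs.

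**The case against.** **The fallback is conditional.** It applies only if the log transformation does not sufficiently correct skew or kurtosis. A reader might infer that it is bound to be reached, because follow-up zeros cannot be normalised. The documents do not support that. Section 4.10.3 names skew and kurtosis and sets no cut-off or formal normality test. In no-effect simulations with 18–30% zeros, 71–81% of samples had absolute skew and excess kurtosis below 1 after log10(x+1), although 59–98% failed a Shapiro-Wilk test. Those cut-offs are assumed. Whether the fallback is reached is open.

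**The model can sometimes be fitted.** A reader might infer that it cannot be fitted at all. That holds for a logit model with categorical time. The protocol's reference to trajectories reads naturally as a time trend, and with linear time the estimates are usually finite. The link and time coding for a binary outcome may be in an analysis plan that is not shown.

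**Significance is not assured.** A reader might infer that a significant reduction is close to guaranteed. That is right for an observed fall only. If behaviour is very stable, McNemar is significant in only 2% of cases, and section 4.5 recruits from venues where men who regularly have unprotected sex are over-represented, so high persistence is plausible. If the six sessions span less than 3 months (their spacing is not stated), the post-intervention recall window also reaches back before the intervention, which shrinks the fall at that visit, though not at the 3-month follow-up.

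**This is a one-arm Phase II study.** Efficacy is explicitly deferred, and no single-arm analysis can fully separate effect from regression to the mean. That stands, and it lowers the severity. It does not excuse a fallback that makes the problem much larger than the count analysis does, when the effect size is the study's main product.

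**Conclusion.** The point holds in a limited form. Sections 4.3 and 4.10.3 together fix the dichotomised baseline at about 100%, so the fallback can show only no change or a fall, produces complete separation at baseline in a logit model with categorical time, and in this single-arm design cannot distinguish an intervention effect from regression to the mean. Without any effect, an observed fall is near-certain unless behaviour is extremely stable: its probability passes 95% at a lapse rate of about 7% (1 − 0.93^42 = 95.3%). The chance of a significant fall cannot be fixed from the documents, because it turns on an unstated lapse rate and on a test the protocol does not name.

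Separately, the hypothesis in section 3.0 (prevalence) does not match the primary endpoint in section 4.9.3 (frequency). This inconsistency stands whether or not the fallback is used.

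**What to change.** - **Section 4.10.3:** remove the dichotomisation fallback. Analyse the 3-month UAI count at all time points with a negative-binomial mixed model or GEE (log link), which needs no normalising transformation, and report the rate ratio for 3-month follow-up versus baseline with its confidence interval.
- **Section 3.0:** reword the hypothesis from reduced prevalence to reduced frequency, to match section 4.9.3.
- **Any binary result:** report only the proportion with no UAI at follow-up, with an exact confidence interval, and not as a change from baseline.
- **Limitation to state:** selection on a baseline count of at least 1 still biases the count ratio modestly towards a decline, so the estimate carried to the randomised trial must be read with that in mind.

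The cost is wording and slightly more analysis work; the data collected do not change. The effect will look less favourable than a fall from 100%.
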